## Abstract

**Background:**

Recent evidence underscores the utility of rapid-acting antidepressant interventions, such as ketamine, in alleviating symptoms of major depressive episodes (MDE). However, to date, there have been limited head-to-head comparisons of intravenous (IV) ketamine infusions with other antidepressant treatment strategies in large randomized trials. This study protocol describes an ongoing multi-centre, prospective, randomized, crossover, non-inferiority trial comparing acute treatment of individuals meeting diagnostic criteria for a major depressive episode (MDE) with ketamine and electroconvulsive therapy (ECT) on efficacy, speed of therapeutic effects, side effects, and health care resource utilization. A secondary aim is to compare a 6-month maintenance strategy for ketamine responders to standard of care ECT maintenance. Finally, through the measurement of clinical, cognitive, neuroimaging, and molecular markers we aim to establish predictors and moderators of treatment response as well as treatment-elicited effects on these outcomes.

**Methods:**

Across four participating Canadian institutions, 240 patients with major depressive disorder or bipolar disorder experiencing a MDE are randomized (1:1) to a course of ECT or racemic IV ketamine (0.5 mg/kg) administered 3 times/week for 3 or 4 weeks. Non-responders (< 50% improvement in Montgomery-Åsberg Depression Rating Scale [MADRS] scores) crossover to receive the alternate treatment. Responders during the randomization or crossover phases then enter the 6-month maintenance phase during which time they receive clinical assessments at identical intervals regardless of treatment arm. ECT maintenance follows standard of care while ketamine maintenance involves: weekly infusions for 1 month, then bi-weekly infusions for 2 months, and finally monthly infusions for 3 months (returning to bi-weekly in case of relapse). The primary outcome measure is change in MADRS scores after randomized treatment as assessed by raters blind to treatment modality.

**Discussion:**

This multi-centre study will help identify molecular, imaging, and clinical characteristics of patients with treatment-resistant and/or severe MDEs who would benefit most from either type of therapeutic strategy. In addition to informing clinical practice and influencing health care delivery, this trial will add to the robust platform and database of CAN-BIND studies for future research and biomarker discovery.

**Trial registration:**

ClinicalTrials.gov identifier NCT03674671. Registered September 17, 2018.

## Background

Worldwide, major depressive disorder (MDD) carries the largest burden of disease among psychiatric, neurological, and substance-use disorders, according to the World Health Organization [1]. Adding to this burden is bipolar disorder (BP), in which patients spend most of their symptomatic time in a major depressive episode (MDE) rather than in a hypomanic or manic episode [2, 3]. Although there are various effective treatments for MDEs, a large proportion of patients do not achieve remission even after several medication trials, and significant responses usually occur after a delay of a few weeks [4]. Thus, there remain major unmet needs for treating MDEs, including higher response rates and treatments that elicit faster antidepressant effects.

Ketamine, a primarily glutamatergic *n*-methyl-D-aspartate (NMDA) receptor antagonist, appears poised to address these needs. The discovery of the rapid antidepressant effects of subanaesthetic doses of intravenous (IV) ketamine [5] has been described as one of the most important breakthroughs in the field of depression in the past 50 years [6]. Randomized, placebo-controlled trials in unipolar and bipolar depression indicate that the antidepressant response to single ketamine infusions often manifests within a few hours, is generally maximal after 24 h, and yet dissipates within 7 days [7, 8]. While the effects of a single infusion are transient, repeated infusions have sustained antidepressant effects [9]. Moreover, our group and others have reported cumulative antidepressant effects with repeated infusions that lead to increased patient response rates over time [10–12], with further prolongation with once-weekly maintenance infusions in previously treatment-resistant depression [10]. Overall, ketamine appears to yield higher response rates than other pharmacological treatment strategies for depression; however, only a few randomized controlled trials have directly compared ketamine with other antidepressant interventions [13, 14].

Electroconvulsive therapy (ECT) remains the gold standard in treating severe and/or treatment-resistant MDEs [15]. Response rates to ECT are high (50–80%), and latency to response is shorter than for classical pharmacotherapy [16–18]. Despite these benefits, access to ECT is limited and lengthy wait-lists are common. Moreover, its high costs, potential for side effects, including cognitive deficits, and enduring stigma have resulted in underutilization of ECT as a treatment for MDEs.

One of the current goals in psychiatry is the identification of biological phenotypes (or biomarkers) that could improve characterization of the likelihood that a patient will respond to a specific treatment strategy. This is particularly pertinent in context of ECT or ketamine treatment, as both are currently reserved for the most treatment resistant and severely depressed patients. Candidate biomarkers for outcome prediction in depression include structural and functional neuroimaging profiles, as well as genetic, epigenetic, proteomic, and metabolic features [19]. Currently, it is unclear how baseline biomarker measures moderate clinical outcomes. Exploring how these measures are impacted by ECT or ketamine may further our understanding of the underlying mechanisms of action of these interventions in alleviating depressive symptoms.

The primary objective of this longitudinal, multi-centre non-inferiority trial is to compare acute treatment of MDEs with repeated IV ketamine and ECT in terms of efficacy, speed of therapeutic effects, side effect profiles, and health care resource utilization. A secondary objective is to assess whether ketamine response can be sustained with a gradual spacing of ketamine maintenance infusions, as is the case for ECT. Finally, through the collection of clinical, cognitive, neuroimaging and molecular data according to Canadian Biomarker Integration Network in Depression (CAN-BIND) protocols [20, 21], we aim to identify biomarkers that predict or moderate ketamine or ECT response.

## Methods/design

### Protocol overview

The study design is a multi-centre, prospective, longitudinal, randomized, crossover, non-inferiority trial comparing ECT and IV ketamine infusions (Fig. 1). After being referred for and consenting to ECT, individuals with MDD or BP currently experiencing a MDE are then offered the opportunity to enroll in this study. Participants who consent are randomized to ECT or ketamine by the site coordinator using a computerized randomization sequence stratified by centre with a 1:1 allocation using random block sizes. During the randomized treatment phase, participants receive a course of thrice-weekly ECT or ketamine infusions for 3 or 4 weeks. Non-responders to the first randomized treatment (< 50% reduction in depression severity as assessed by blinded raters using the Montgomery-Åsberg Depression Rating Scale [MADRS] [22], and MADRS score ≥ 22) crossover to receive treatment with the second strategy. Participants continue taking any concomitant medication throughout the study, with no change in medication regimen permitted during the initial randomization or crossover phase. Individuals who achieve response (≥ 50% reduction in MADRS scores and MADRS score < 22) in either the randomized treatment or crossover phase are eligible to enter the maintenance phase, while treatment non-responders following the crossover phase exit the study. During the 6-month maintenance phase, ECT is administered at the discretion of the prescribing physician as per standard of care, while ketamine is administered according to a set schedule. Clinical, cognitive and molecular assessments are conducted at baseline (prior to treatment initiation), post-randomized treatment phase (following weeks 3 or 4), post-crossover phase (if present), and mid- and post-maintenance phase. Neuroimaging occurs at baseline, post-randomized treatment phase, and mid-maintenance (imaging occurs less frequently due to cost and increased participant burden). As part of the CAN-BIND Integrated Discovery Program, this trial is principally funded by the Ontario Brain Institute (OBI). The lead site overseeing the clinical trial is the Royal’s Institute of Mental Health Research (IMHR), affiliated with the University of Ottawa and the Principal Investigator is [name].

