### Participants

A total of 240 participants are being recruited at four centres in Canada: Ottawa (Royal Ottawa Mental Health Centre), Toronto (University Health Network), Kingston (Providence Care Hospital), and Montreal (Douglas Mental Health University Institute). The research ethics boards at each site have approved the study protocol. Participants are being recruited directly from ECT service waitlists and referrals at each participating hospital. Enrollment is expected to last 3 years from the first patient enrolled. Table 1 lists the inclusion and exclusion criteria for participants.

**Table 1 Tab1:** Inclusion and exclusion criteria for participants

*Inclusion criteria*	
• Ability to freely provide written informed consent before initiation of study related procedures.	
• Inpatients or outpatients referred to and eligible for standard ECT. Willing to accept randomization to either ECT or IV ketamine arms.	
• Males and females between 18 and 70 years of age.	
• Meet Diagnostic and Statistical Manual for Mental Disorders, fifth edition (DSM-5) [23] criteria for MDD or BP without psychotic symptoms as confirmed by the MINI International Neuropsychiatric Interview (MINI) [24].	
• Currently in a MDE confirmed by the MINI.	
• Montgomery-Åsberg Depression Rating Scale (MADRS) [22] total score of ≥26 at screening and at randomization, with no more than 20% improvement between these two visits.	
• Body mass index < 35.	
• Montreal Cognitive Assessment (MOCA) [25] score ≥ 24.	
• Ability to understand and comply with study requirements, as judged by the investigator(s).	
*Exclusion criteria*	
• Depression secondary to stroke, cancer or other medical illnesses.	
• Prior or current substance abuse or dependence (except for caffeine or nicotine dependence) and/or recent history (last 12 months) of current alcohol abuse or dependence, as defined by DSM-5 criteria [23].	
• A positive toxicology screen for drugs that are not prescribed.	
• Pregnant, breastfeeding, or of childbearing potential and not willing to use an approved method of contraception during the study.	
• Evidence of clinically relevant disease or unstable medical illness.	
• Clinically significant deviation from reference ranges in clinical laboratory tests.	
• Clinically significant electrocardiogram results as judged by the investigator(s) or cardiologist.	
• History of seizure disorder, except febrile convulsions.	
• Known history of intolerance or hypersensitivity to ketamine.	

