### Treatment schedule

#### Randomized treatment phase

For participants receiving ECT, the number of treatments (9 or 12) is determined by the treating physician. For the ketamine arm, the number of treatments is determined by participants’ antidepressant response as assessed using the MADRS. Participants achieving remission (MADRS ≤10) after 9 ketamine infusions exit the randomized treatment phase and are eligible to enter the maintenance phase (Fig. 1). Participants receiving ketamine who achieve an antidepressant response but not remission after 9 treatments receive an additional 3 infusions (12 treatments total). In both treatment arms, non-responders (< 50% MADRS decrease or a score ≥ 22) after 3 weeks may crossover to receive a full course of treatment with the alternative strategy. Responders after 12 treatments may move on to the maintenance phase.

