#### Crossover phase

Participants only enter the crossover phase if they do not meet antidepressant response criteria at the end of the randomized treatment phase. During the crossover phase, ECT non-responders receive a course of 9 or 12 ketamine infusions, while ketamine non-responders undergo 9 or 12 ECT sessions. Non-responders at the end of the crossover phase exit the study. Those meeting the response criteria after the crossover phase (≥ 50% MADRS score decrease relative to pre-crossover score and MADRS score < 22) may enter the maintenance phase.

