#### Maintenance phase

Treatment during the maintenance phase lasts 6 months from entry (immediately after completion of the randomized treatment or crossover phase), with a follow-up assessment at month 7. ECT maintenance follows standard of care wherein the treating physician will determine if the participant will receive ECT maintenance, and if so, the frequency of these treatments in accordance with patients’ needs and Canadian Network for Mood and Anxiety Treatments (CANMAT) 2016 Clinical Guidelines [15]. Participants undergoing ketamine maintenance treatment receive infusions according to the following schedule: 1 infusion per week for the first 4 weeks, followed by 1 infusion every 2 weeks for 2 months, and then 1 infusion every month for 3 months. Individuals who experience a relapse of depressive symptoms (MADRS ≥22 or loss of 50% improvement from baseline) with monthly ketamine infusions may return to bi-weekly infusions for the remainder of the maintenance phase. Participants who fail to meet response criteria at any two consecutive study visits during the maintenance phase discontinue treatments (if present) and exit the study. At the conclusion of study participation, all participants have a final follow-up visit and are discharged to their referring physician with treatment recommendations.

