### Data analyses

The primary outcome measure is the rate of antidepressant response (i.e., percentage of participants meeting antidepressant response criteria [≥ 50% reduction in MADRS scores from baseline and MADRS score < 22]) in each arm at the end of the randomized treatment phase. A total of 240 participants will be enrolled into the randomized treatment phase across the four recruiting sites. This will allow for a 20% drop-out rate (i.e., withdrawal of approximately 40 participants), resulting in a total sample of *N* = 200. For the primary efficacy analyses, a non-inferiority margin of 20% was selected based on clinical judgment. Thus, a sample of 200 participants (*N* = 100/treatment arm) is required to be 90% certain that the upper limit of a one-sided 95% confidence interval will exclude a difference in favour of the ECT group of more than 20%. Secondary efficacy outcomes will include percent change in MADRS scores from baseline to the end of the randomized treatment phase, and remission rates (MADRS score ≤ 10). Response and remission rates will also be assessed for the crossover phase. Clinical scores will be analyzed using linear mixed models (appropriate covariates, such as site, will be included, as needed). Categorical outcomes (response/remission) will be examined using χ^2^ tests. The alpha will be set at 0.05.

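### The Protocol overview defines crossover non-response with *and* where the treatment schedule uses *or*, so it is not the complement of the responder rule

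*Protocol article*

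**What the plan says.** The Protocol article states the rule for leaving the randomized phase in several places.

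- **Protocol overview, non-responders:** less than a 50% reduction on blinded MADRS ratings "and MADRS score ≥ 22) crossover to receive treatment with the second strategy". Both conditions must hold.
- **Protocol overview, responders:** "Individuals who achieve response (≥ 50% reduction in MADRS scores and MADRS score < 22"). Both conditions must hold. Data analyses uses the same pair of conditions for the primary endpoint.
- **Randomized treatment phase:** "non-responders (< 50% MADRS decrease or a score ≥ 22) after 3 weeks may crossover". Either condition is enough.
- **Crossover phase:** "Participants only enter the crossover phase if they do not meet antidepressant response criteria at the end of the randomized treatment phase".
- **Maintenance phase, relapse:** "MADRS ≥22 or loss of 50% improvement from baseline". Either condition is enough.

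Table 1 sets the lowest possible baseline, a MADRS "total score of ≥26 at screening and at randomization". Data analyses adds that "Response and remission rates will also be assessed for the crossover phase".

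**The concern.** The Protocol overview and the Randomized treatment phase section give different rules for the same decision: whether a patient who has finished the first treatment may receive the other one. The overview also conflicts with its own responder definition. When response needs two conditions together, failing either one is non-response. The overview instead asks for both to fail.

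A patient who fails exactly one condition then has no label. That patient cannot enter maintenance, which requires response, and under the overview cannot cross over either. At stake are the offer of the alternative treatment to a patient who has not responded, the group in which crossover response and remission are estimated, and the part of the maintenance cohort that arrives through crossover.

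**Working it through.** The plan gives no figure to reproduce here. The check is one of logic, followed by an enumeration of scores.

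**Inputs.** The response, overview and treatment-schedule rules are as given above. The minimum baseline is 26 (Table 1). The maximum score of 60 is an assumption, because the document says only that the MADRS has 10 items. Let b be the baseline score and e the score at the end of the randomized phase, both integers.

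**Step 1: the complement.** Response is (reduction ≥ 50%) and (e < 22). By De Morgan's law its negation is (reduction < 50%) or (e ≥ 22). That is the Randomized treatment phase rule. The overview rule, (reduction < 50%) and (e ≥ 22), is strictly narrower.

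**Step 2: who falls between.** Under the overview, a patient is unclassified if exactly one response condition fails.

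*Group (a): reduction < 50% but e < 22.* A reduction below 50% means e > b/2, so b/2 < e ≤ 21.
- b = 26: e from 14 to 21.
- b = 30: e from 16 to 21. Going from 30 to 18 is a reduction of 12/30 = 40%.
- b = 41: e = 21 only.
- b = 42: e would have to exceed 21, so there are none.

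The group therefore exists for baselines 26 to 41 with end scores 14 to 21.

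*Group (b): reduction ≥ 50% but e ≥ 22.* This needs 22 ≤ e ≤ b/2, hence b ≥ 44.
- b = 44: e = 22 only.
- b = 46: e = 22 or 23. Going from 46 to 23 is a reduction of 23/46 = 50%.
- b = 50: e from 22 to 25.

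**Step 3: all score pairs.** Baselines 26 to 60 and end scores 0 to 60 give 35 × 61 = 2,135 pairs.

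| Overview wording | Group (a) | Group (b) | Unclassified |
|---|---|---|---|
| *and* (as written) | 72 | 81 | 153 |
| *or* (as in the treatment schedule) | 0 | 0 | 0 |

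The pair counts show that the gap is real and that *or* closes it completely. They are not patient frequencies, since the document gives no MADRS distribution with which to weight them.

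**Step 4: which text is the outlier.** The Randomized treatment phase rule matches the complement of response in every pair. The relapse rule in the Maintenance phase section also uses *or*. The Crossover phase section makes failure to meet the response criteria a condition for entry. Every patient caught by the overview's *and* rule meets that condition, so this section does not contradict the overview. The direct conflict is between the overview and the Randomized treatment phase section.

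**The case against.** The strongest reply is that the operative text already settles the matter. The faulty sentence stands in an overview. The detailed rule is in the treatment schedule and is correct, and Data analyses defines response consistently with it. A site working from the treatment schedule would class a patient going from 30 to 18 as a non-responder who may cross over. This stands, and it makes the point a wording error rather than a missing rule. It does not remove the error: the article gives two incompatible rules for one decision about a patient's treatment, and condensing a fuller protocol excuses omission but not contradiction.

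Three stronger readings are tempting, and the document does not support them.

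- A reader might infer that the Crossover phase section admits everyone who fails response and so contradicts the overview as well. Its wording makes non-response necessary for entry, not sufficient.
- A reader might infer a third rule from the abstract, where those with less than 50% improvement in MADRS "scores) crossover to receive the alternate treatment". An abstract is shorthand, and leaving out the score threshold there is ordinary condensation.
- A reader might infer that patients have already been misrouted. Fig. 1 and the full protocol are not shown, and nothing in the article says that any site worked from the overview wording.

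**Conclusion.** The contradiction is real and the overview is the text in error. Followed literally, it would leave patients in groups (a) and (b) with neither crossover nor maintenance. Group (a) begins at the entry minimum of 26 and includes ordinary partial improvement, so the gap is not confined to extreme scores. The existence of both groups follows from the stated rules. Only the upper end of group (b) depends on the assumed scale maximum of 60.

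The number of patients affected cannot be derived from the document, and any percentage would rest on an assumed distribution of baseline scores and improvement. The primary endpoint is unaffected because it is defined through the response rule. Direct entry to maintenance from the randomized phase is unaffected because it requires response under either wording. The possible effect is confined to who is offered the second treatment, the crossover response and remission rates, and the crossover responders who go on to maintenance. Severity is minor.

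**What to change.** In the Protocol overview, change *and* to *or* in the non-responder definition, so that non-response is a reduction below 50% or a score of 22 or more. Confirm to the four sites that the rule in the Randomized treatment phase section governs crossover entry. The cost is one word and a short clarification note. Sample size, visits, maintenance eligibility and the primary analysis stay as they are.

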**Fig. 1 Fig1:**
[figure not shown]
Study design

### Participants

A total of 240 participants are being recruited at four centres in Canada: Ottawa (Royal Ottawa Mental Health Centre), Toronto (University Health Network), Kingston (Providence Care Hospital), and Montreal (Douglas Mental Health University Institute). The research ethics boards at each site have approved the study protocol. Participants are being recruited directly from ECT service waitlists and referrals at each participating hospital. Enrollment is expected to last 3 years from the first patient enrolled. Table 1 lists the inclusion and exclusion criteria for participants.

**Table 1 Tab1:** Inclusion and exclusion criteria for participants

*Inclusion criteria*	
• Ability to freely provide written informed consent before initiation of study related procedures.	
• Inpatients or outpatients referred to and eligible for standard ECT. Willing to accept randomization to either ECT or IV ketamine arms.	
• Males and females between 18 and 70 years of age.	
• Meet Diagnostic and Statistical Manual for Mental Disorders, fifth edition (DSM-5) [23] criteria for MDD or BP without psychotic symptoms as confirmed by the MINI International Neuropsychiatric Interview (MINI) [24].	
• Currently in a MDE confirmed by the MINI.	
• Montgomery-Åsberg Depression Rating Scale (MADRS) [22] total score of ≥26 at screening and at randomization, with no more than 20% improvement between these two visits.	
• Body mass index < 35.	
• Montreal Cognitive Assessment (MOCA) [25] score ≥ 24.	
• Ability to understand and comply with study requirements, as judged by the investigator(s).	
*Exclusion criteria*	
• Depression secondary to stroke, cancer or other medical illnesses.	
• Prior or current substance abuse or dependence (except for caffeine or nicotine dependence) and/or recent history (last 12 months) of current alcohol abuse or dependence, as defined by DSM-5 criteria [23].	
• A positive toxicology screen for drugs that are not prescribed.	
• Pregnant, breastfeeding, or of childbearing potential and not willing to use an approved method of contraception during the study.	
• Evidence of clinically relevant disease or unstable medical illness.	
• Clinically significant deviation from reference ranges in clinical laboratory tests.	
• Clinically significant electrocardiogram results as judged by the investigator(s) or cardiologist.	
• History of seizure disorder, except febrile convulsions.	
• Known history of intolerance or hypersensitivity to ketamine.	

